## Abstract

**Background:**

Current treatments for Alzheimer's disease and related disorders (ADRD) are symptomatic and can only temporarily slow down ADRD. Future possibilities of care rely on multi-target drugs therapies that address simultaneously several pathophysiological processes leading to neurodegeneration. We hypothesized that the combination of memantine with vitamin D could be neuroprotective in ADRD, thereby limiting neuronal loss and cognitive decline. The aim of this trial is to compare the effect after 24 weeks of the oral intake of vitamin D_3 _(cholecalciferol) with the effect of a placebo on the change of cognitive performance in patients suffering from moderate ADRD and receiving memantine.

**Methods:**

The AD-IDEA Trial is a unicentre, double-blind, randomized, placebo-controlled, intent-to-treat, superiority trial. Patients aged 60 years and older presenting with moderate ADRD (i.e., Mini-Mental State Examination [MMSE] score between 10-20), hypovitaminosis D (i.e., serum 25-hydroxyvitamin D [25OHD] < 30 ng/mL), normocalcemia (i.e., serum calcium < 2.65 mmol/L) and receiving no antidementia treatment at time of inclusion are being recruited. All participants receive memantine 20 mg once daily -titrated in 5 mg increments over 4 weeks- and each one is randomized to one of the two treatment options: either cholecalciferol (one 100,000 IU drinking vial every 4 weeks) or placebo (administered at the same pace). One hundred and twenty participants are being recruited and treatment continues for 24 weeks. Primary outcome measure is change in cognitive performance using Alzheimer's Disease Assessment Scale-cognition score. Secondary outcomes are changes in other cognitive scores (MMSE, Frontal Assessment Battery, Trail Making Test parts A and B), change in functional performance (Activities of Daily Living scale, and 4-item Instrumental Activities of Daily Living scale), posture and gait (Timed Up & Go, Five Time Sit-to-Stand, spatio-temporal analysis of walking), as well as the between-groups comparison of compliance to treatment and tolerance. These outcomes are assessed at baseline, 12 and 24 weeks, together with the serum concentrations of 25OHD, calcium and parathyroid hormone.

**Discussion:**

The combination of memantine plus vitamin D may represent a new multi-target therapeutic class for the treatment of ADRD. The AD-IDEA Trial seeks to provide evidence on its efficacy in limiting cognitive and functional declines in ADRD.

**Trial Registration:**

ClinicalTrials.gov number, NCT01409694

## Background

Alzheimer's disease (AD) is the leading cause of dementia and loss of autonomy and independency in the elderly [1,2]. AD is characterized by a progressive decline of cognitive performance with a deleterious impact on social activities. The magnitude of this problem will increase over the next decades due to the demographic shift of the aging population. In order to mitigate and delay AD-related adverse effects, the development of new effective therapeutic strategies is essential [1,2].

In addition to a decrease in brain cholinergic activity that justifies the use of acetylcholinesterase inhibitors [1], AD is also marked by glutamatergic excitotoxicity [3,4] that results in neuronal death through two distinct mechanisms: immediate neuronal necrosis in the case of excessive intraneuronal calcium influx, and delayed neuronal apoptosis in the case of moderately excessive calcium influx with subsequent oxidative stress [5,6]. The clinical consequence of these chain reactions for glutamatergic neurons is the loss of learning and memory abilities characterizing dementia syndromes including AD and related disorders (ADRD) [1,3,4].

These pathophysiologic mechanisms explain why one of the most prescribed drugs to slow the progression of ADRD is memantine; a voltage-dependent, low-affinity, noncompetitive N-methyl-D-aspartate (NMDA) receptor antagonist [7,8]. The effectiveness of this drug was established in double-blind placebo-controlled trials in moderate to severe stages of dementia. Memantine has no immediate treatment effect, but after 3 to 6 months of use, patients report better cognitive performance and autonomy than those receiving placebo [7,8]. However, symptom improvement is transient and the memory scores then adopt a similar course to those in the placebo group [9]. Indeed, the use of memantine may result in the protection of glutamatergic neurons associated with the avoidance of neuronal necrosis phenomena subsequent to the excessive and prolonged influx of calcium into the cell, but AD patients using memantine are still exposed to oxidative stress and neuronal apoptosis. Thus, while NMDA receptor antagonists such as memantine allow symptomatic treatment of AD by temporarily slowing disease progression, they do not allow a preventive or curative treatment [7,8]. Coupling an antioxidant with memantine could therefore provide a solution to the problem of neuronal apoptosis induced by glutamatergic excitotoxicity.

Vitamin D is a neurosteroid hormone which crosses the blood-brain barrier and binds to vitamin D receptors (VDR) present in neurons and glial cells of the central nervous system including the hippocampus, the hypothalamus, the cortex and the subcortex [10-12]. More precisely, 1.25-dihydroxyvitamin D (active form of vitamin D) regulates the intra-neuronal calcium homeostasis via the regulation of voltage-gated calcium channels - thus preventing necrosis - [13], and has also exhibited neuroprotective properties against glutamate toxicity through antioxidant effects - thus preventing apoptosis. This antioxidant action was described in 2001 in cultures of rat mesencephalic cells [14]. This is particularly important in that over 70% of adults aged 75 and over are deficient in vitamin D [15,16] and should receive vitamin D supplementation, and especially since vitamin D deficiency has been associated with cognitive decline [10,17-20]. Thus, based on the neurosteroid properties of vitamin D, it can be argued that the correction of hypovitaminosis D may be protective against cognitive decline [11,20-23]. For illustration, it has already been shown that high exogenous supplies of vitamin D were associated with better cognitive performance compared to lower supplies [21,22]. What is more, it is interesting to note that the actions of vitamin D on the nervous system seem to be complementary and perfectly suited to those of memantine, and there is no reason to expect a deleterious interaction of these molecules [11].

Finally, the known actions of both these molecules are not reduced to learning and memory, but also improves physical performance. Indeed, each molecule taken separately has already been associated with an improvement of gait [24-26]. This is especially important since one of the main complication of ADRD relies on motor dysfunction illustrated by chronic gait disorders and loss of functional independence [2,27]. The expected improvement of cognitive performance in ADRD patients receiving both memantine and vitamin D could thus be accompanied by improved posture and gait performance.

We hypothesized that the combination of memantine plus vitamin D could be more protective in ADRD than taking memantine alone against the neuronal loss and the subsequent declines in cognitive and gait performance.

## Objectives

### Primary objective

The primary objective is to compare the effect after 24 weeks of the oral intake of vitamin D_3 _with the effect of a placebo on the evolution of cognitive performance in patients suffering from moderate ADRD and receiving memantine.

### Secondary objectives

The secondary objectives of the study are as follows:

- To compare the effect after 12 weeks of the oral intake of vitamin D_3 _with the effect of a placebo on the evolution of cognitive performance in patients suffering from moderate ADRD and receiving memantine.

- To compare the effect after 12 and 24 weeks of the oral intake of vitamin D_3 _with the effect of a placebo on the evolution of functional abilities in patients suffering from moderate ADRD and receiving memantine.

- To compare the effect after 12 and 24 weeks of the oral intake of vitamin D_3 _with the effect of a placebo on the evolution of postural and gait performance in patients suffering from moderate ADRD and receiving memantine.

- To determine the compliance to treatment and tolerancy of the oral intake of vitamin D_3 _in patients suffering from moderate ADRD and receiving memantine.

## Methods

### Design

This is a unicentre, double-blind (with patient, carer, clinician, outcome assessor and investigators blinded), randomized, placebo-controlled, parallel group, intent-to-treat, superiority clinical trial. Figure 1 illustrates the trial design and Table 1 summarizes the timing of the trial. All participants receive trial interventions for 24 weeks as recommended by the European Medicines Agency (EMEA) guidelines [28]. The randomization is stratified depending on the nature of dementia (i.e., Alzheimer's disease [AD], or related disorders [RD]). Thus, for each stratum (2 strata), a distinct randomization list is established by the Clinical Research Centre (CRC) of Angers with the use of the N'Query randomization software. In order to best limit potential imbalances, a block randomization is used.

**Figure 1 F1:**
[figure not shown]
**Trial flow chart**. Flow chart of the Trial Study.

**Table 1 T1:** Calendar summary

Period	Pre-selection	Inclusion	Follow-up	End of the study
**Week (W)**		**W0**	**W12**	**W24**

Pre-inclusion criteria	X			

Inclusion/Non-inclusion criteria		X		

Informed consent		X		

Inclusion clinical examination	X			

Analysis of posture and gait	X		X	X

Assigning a 'Patient's kit'according to inclusion number in compliance with randomization lists		X		

Serum 25OHD measurement	X		X	X

Serum calcium measurement	X		X	X

Serum parathyroid hormone measurement	X		X	X

Treatment administration		X		

Compliance (account of fully consumed vials)			X	X

Follow-up clinical examination			X	X

Cognitive scores (including ADAS-cog)	X		X	X

Functional scores	X		X	X

AEs and SAEs	X		X	X

Randomization lists were transmitted to the central pharmacy of Angers University Hospital which is in charge of assigning the 'patients' kits' in compliance with the randomization lists, and of shipping the kits containing containing all the medicines for the duration of the study (i.e., 322 tablets of memantine 10 mg, and 6 × 100,000 IU cholecalciferol or placebo vials) to the memory centre of Angers University Hospital. Of these 322 tablets of memantine, 316 are theoretically used during the 24-week follow-up, and an additional 6 tablets (equivalent to 3 days treatment) were added in each kit to be more flexible in determining the date of the final visit.

#### - 'Intervention' group

All participants start the treatment with memantine (Lundbeck Laboratory, Issy-les-Moulineaux, France) on the first day of the study. Memantine is administered according to the usual strategy, with upward titration of 5 mg per week during the first four weeks to reduce the risk of side effects. The final dosage is 20 mg per day, with no subsequent modification of dosage or specialty during the trial. In parallel, the participants of this group immediately commence vitamin D supplementation (cholecalciferol 100,000 IU [Crinex Laboratory, Montrouge, France], drinking solution, 2 mL vial) at a rate of 1 drinking vial of 100,000 IU cholecalciferol every month. In brief, the total dose is 600,000 IU over the study period of 168 days, starting with one vial at the time of inclusion, then at Week (W) 4, W8, W12, W16 and W20. It is generally recognized that each additional 100 IU of vitamin D per day raises serum 25OHD concentration by 0.7 ng/mL [29]. The daily dose of 3,571 IU in the AD-IDEA trial is thus expected to raise the serum 25OHD concentration by at least 25 ng/mL, with a concentration ultimately reached > 30 ng/mL. This is all the more important in that, based on the knowledge of vitamin D effects in organs other than brain, it seems that raising serum 25OHD concentrations above 30 ng/mL is necessary to obtain an effect on non-skeletal targets [30]. We assume that the 24 week assessment will capture a treatment effect since vitamin D supplementation > 6 months is not more effective than shorter treatment ≤ 6 months for the prevention of non-skeletal adverse events [31]. Finally, it has to be quoted that the chosen dose of 3,571 IU per day does not reach toxic doses (i.e., 10,000 IU per day) and raises vitamin D concentrations within non-toxic limits (i.e., 150 ng/mL) [32]. As a consequence, the dose of vitamin D supplementation will not be adjusted except in the case of a serious adverse event such as hypercalcemia, possibly resulting from the intestinal absorption of dietary calcium under the action of vitamin D [16,30]. In this case, vitamin D supplementation is stopped and the participant is released prematurely from the study.

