### Assessments

Study assessment measures will be applied at baseline prior to randomization, at W12 and at W24. All measures in the study are already carried out systematically in every patient admitted to Angers University Memory Centre. Experience has shown that this mode of operation is feasible and appreciated by patients and their families, and has never caused a breakdown in care so far. For this reason, the large number of measures is not expected to exacerbate the loss to follow-up. To ensure adherence to the intervention, nurses are prescribed for all participants to administer medications safely and effectively. In addition, phone calls are planned to keep in touch with the participant and to recall the date of follow-up visits. Trial completion is defined as completion of 24 weeks on the trial medication or discontinuation of follow-up for any cause. Participants who discontinue taking the trial medications are encouraged to remain in follow-up. Arrangements for continued provision of the trial medication at the end of the trial is made on an individual basis thanks to a centralized serum 25OHD measurement at W24 which allows the investigating physician in charge of the patient making rapid and appropriate decisions regarding carrying on, modifying or discontinuing vitamin D supplementation at the end of the study.

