##### - Safety parameters

The safety assessment parameters are:

- Clinical: delirium, somnolence, asthenia, vertigo, headache, epilepsy, nausea and vomiting, heart failure, lumbar or right hypochondre pain in the case of biliary or renal colics revealing calcic lithiasis (objectivized with echography in the case of clinical suspicion), thrombosis (objectivized with doppler in the case of clinical suspicion);

- Biological: serum calcium concentration. The serum concentration of calcium is measured at baseline assessment, then at W12 and W24 to monitor the occurrence of hypercalcemia > 2,65 mmol/L [32]. The occurrence of hypercalcemia leads to double-blind termination and premature withdrawal from the study, stops the vitamin D supplementation and potential calcium supplements, and triggers further complementary non-specific examinations to find the cause of hypercalcemia for which vitamin D intake could not be held responsible at first [16].

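### Hypercalcaemia ends study participation rather than only the vials, so cases found before week 24 lose the primary ADAS-cog score

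*Protocol article*

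**What the plan says.** The rule appears twice in the Methods of the protocol article.

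- The subsection on the intervention group keeps the dose fixed except after a serious adverse event such as hypercalcaemia, described as "possibly resulting from the intestinal absorption of dietary calcium under the action of vitamin D". It then says: "In this case, vitamin D supplementation is stopped and the participant is released prematurely from the study".
- Under Safety parameters, with a threshold of 2.65 mmol/L and no restriction to one arm: "The occurrence of hypercalcemia leads to double-blind termination and premature withdrawal from the study". Stopping vitamin D and any calcium supplements follows as a further consequence.

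On timing, Safety parameters states: "The serum concentration of calcium is measured at baseline assessment, then at W12 and W24 to monitor the occurrence of hypercalcemia". Table 1 schedules ADAS-cog at pre-selection, week 12 and week 24. The primary objective is the 24-week comparison.

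Two other statements bear on the point. Under Assessments: "Participants who discontinue taking the trial medications are encouraged to remain in follow-up". Under Design, the trial is described as a "placebo-controlled, parallel group, intent-to-treat, superiority clinical trial".

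**The concern.** Stopping a treatment and leaving a trial are different events. Under intent-to-treat, a patient who stops the vials for safety should still be measured at week 24 and compared in the arm assigned. Here the safety rule does both at once, so it removes the outcome along with the treatment.

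The loss is also not clearly unrelated to treatment. The article itself names vitamin D as a possible cause of the event that triggers withdrawal. If hypercalcaemia is more frequent on vitamin D, week-24 scores will be missing more often in that arm, and the patients concerned may differ from those who remain. Counting them in the intent-to-treat population does not solve this: a missing score can be modelled, but not recovered.

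There is a safety cost too. Tolerance of vitamin D is a secondary objective, yet the rule ends scheduled calcium and adverse-event assessment in the patients who had the event of interest.

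**Working it through.** **Which cases lose the primary outcome**

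| When hypercalcaemia is found | Consequence under the stated rule | Week-24 ADAS-cog |
|---|---|---|
| Unscheduled test before week 12 | Leaves the study | Not collected; week 12 also lost |
| Week-12 sample | Leaves the study | Not collected; a week-12 score would normally exist |
| Unscheduled test between weeks 12 and 24 | Leaves the study | Not collected |
| Week-24 sample | Already at the final visit | Need not be lost |

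The article does not say in so many words that no week-24 score is taken. That follows from release or withdrawal from the study, and nothing in the text provides for a later ADAS-cog.

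**How easily the trigger is met.** Entry requires calcium below 2.65 mmol/L, and withdrawal follows above 2.65 mmol/L. A patient enrolled just under the limit could therefore be withdrawn after a slight rise.

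**Size of a possible shift.** The article gives no figure for the hypercalcaemia rate, its split between arms, or how affected patients would differ. The range below is an illustration.

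Inputs from Sample Size Calculation: 60 randomised per arm, 52 evaluable per arm, SD 5, target difference 3 points. The 52 per arm serves only as a benchmark for precision; whether it matches the stated power is a separate question.

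Assumptions: a net excess of k = 0 to 3 patients lost before week 24 in one arm, whose 24-week change differs from the rest of that arm by d = 1 to 3 points, in either direction.

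Shift in the arm difference = (k / 60) × d

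| k | d = 1 | d = 3 |
|---|---|---|
| 0 | 0 | 0 |
| 1 | 1/60 × 1 = 0.02 | 1/60 × 3 = 0.05 |
| 2 | 2/60 × 1 = 0.03 | 2/60 × 3 = 0.10 |
| 3 | 3/60 × 1 = 0.05 | 3/60 × 3 = 0.15 |

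Equal loss in both arms with the same d gives no shift.

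- Against the target: 0.15 / 3 = 5%.
- Standard error of the difference: 5 × √(2/52) = 0.98.
- Against the standard error: 0.15 / 0.98 = 0.15.

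**A harsher case.** Suppose 10% of the vitamin D arm (6 of 60) and none of the placebo arm were lost, with d = 3. The shift is 0.10 × 3 = 0.30 points, which is 10% of the target.

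**Power.** With the planned 15% loss, 60 × 0.85 = 51 remain per arm, and power for 3 points is 85.8% (normal approximation, two-sided 5%). With a further 10% lost in the vitamin D arm only, 51 × 0.90 = 45.9 remain there:

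- SE = 5 × √(1/45.9 + 1/51) = 1.02
- power = Φ(3/SE − 1.96) = 83.9%

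Even here the cost is about 2 percentage points. The issue is possible imbalance in what is missing more than loss of numbers.

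**The case against.** The strongest reply is that the two rules can coexist. Encouraging follow-up after stopping medication is the general policy, and hypercalcaemia is a specific safety exception. The Assessments section also anticipates early exits: "Trial completion is defined as completion of 24 weeks on the trial medication or discontinuation of follow-up for any cause". Release from the study may be loose wording in a condensed article, with post-withdrawal visits and missing-data handling set out in the full protocol. Intent-to-treat concerns analysis by assigned arm, and nothing excludes these patients from analysis.

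There are also reasons to expect few cases. Patients with severe renal failure or a contra-indication to vitamin D are excluded. The dose of 3,571 IU per day is well below the 10,000 IU per day that the article calls toxic. Safety parameters does not presume that vitamin D is the cause. Finally, 15% loss to follow-up is already allowed for.

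Part of this stands. The exception reading is coherent, the number affected may be very small, and an excess on vitamin D is plausible but not established. It does not remove the point, for these reasons:

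- Even as a deliberate exception, the rule gives up the primary outcome after an event that may be related to treatment. Stopping the vials and investigating the cause already deals with the exposure, without ending outcome collection.
- Loose wording is an unlikely explanation, because both places list stopping vitamin D and leaving the study as separate consequences.
- This is a stated conduct rule, not a missing analysis detail, and later handling of missing data cannot restore an uncollected score. A week-12 or exit score is not a week-24 score.
- The 15% allowance protects the sample size, not the balance of what is lost.

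**Conclusion.** The concern holds. As written, hypercalcaemia found before week 24 removes the participant from the study and, with that, the primary outcome. This is at odds with the article's own policy for patients who stop medication and weakens the intent-to-treat comparison.

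The expected effect is small: 0 to ±0.15 ADAS-cog points under the main assumptions, and 0.30 in the harsher case. All of these rest on assumed counts and differences, and neither the direction of any bias nor the arm split is known. Nothing here suggests that the rule alone would overturn the trial's conclusion. It should be fixed because the loss is avoidable and cannot be repaired afterwards.

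**What to change.** In the intervention-group subsection and under Safety parameters, separate stopping the study vials from leaving follow-up:

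- Keep the clinical rule. On hypercalcaemia, stop the vitamin D or placebo vials and any calcium supplements, and investigate the cause.
- Continue the scheduled week-12 and week-24 ADAS-cog and safety assessments unless consent is withdrawn.
- Analyse the participant in the assigned arm.
- If the treatment code is broken, keep the ADAS-cog rater blind to it.
- As a minor point, align the definition of trial completion under Assessments, so that completing follow-up is distinct from completing treatment.

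The cost is a short protocol amendment, revised case report form wording, and a few visits that are already in the schedule. The article gives the trial status as recruiting, so the change could still apply to patients not yet enrolled.

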#### - 'Placebo' group

Participants in this arm start the treatment with memantine at the same rate as the 'Intervention' group. They also immediately start cholecalciferol placebo (Placebo [Crinex Laboratory, Montrouge, France], drinking solution, 2 mL vial) administered at the same pace (i.e., W0, W4, W8, W12, W16 and W20). The placebo drinking solution contains all the excipients present in the cholecalciferol vial and is not distinguishable from the active product (vitamin D).

Regardless of groups, enrolled participants are also provided with oral and written information that they cannot, in any case, be prescribed medication containing vitamin D or memantine or acetylcholinesterase inhibitors outside of the trial for the duration of the study.

